## Abstract

**Background:**

Intracranial hemorrhage occurs in over 60% of severe head injuries in one of three types: extradural (EDH); subdural (SDH); and intraparenchymal (TICH). Prompt surgical removal of significant SDH and EDH is established and widely accepted. However, TICH is more common and is found in more than 40% of severe head injuries. It is associated with a worse outcome but the role for surgical removal remains undefined. Surgical practice in the treatment of TICHs differs widely around the world. The aim of early surgery in TICH removal is to prevent secondary brain injury. There have been trials of surgery for spontaneous ICH (including the STICH II trial), but none so far of surgery for TICH.

**Methods/Design:**

The UK National Institutes of Health Research has funded STITCH(Trauma) to determine whether a policy of early surgery in patients with TICH improves outcome compared to a policy of initial conservative treatment. It will include a health economics component and carry out a subgroup analysis of patients undergoing invasive monitoring. This is an international multicenter pragmatic randomized controlled trial.

Patients are eligible if: they are within 48 h of injury; they have evidence of TICH on CT scan with a confluent volume of attenuation significantly raised above that of the background white and grey matter that has a total volume >10 mL; and their treating neurosurgeon is in equipoise.

Patients will be ineligible if they have: a significant surface hematoma (EDH or SDH) requiring surgery; a hemorrhage/contusion located in the cerebellum; three or more separate hematomas fulfilling inclusion criteria; or severe pre-existing physical or mental disability or severe co-morbidity which would lead to poor outcome even if the patient made a full recovery from the head injury.

Patients will be randomized via an independent service. Patients randomized to surgery receive surgery within 12 h. Both groups will be monitored according to standard neurosurgical practice. All patients have a CT scan at 5 days (+/−2 days) to assess changes in hematoma size. Follow-up is by postal questionnaire at 6 and 12 months. The recruitment target is 840 patients.

**Trial registration:**

Current Controlled Trials ISRCTN19321911

## Background

More than 150,000 patients with head injury are admitted to hospital each year in the UK. Of these about 20,000 are serious. One year after a serious head injury 35% of patients are dead or severely disabled. Intracranial hemorrhage occurs in more than 60% of serious head injuries in one or more of three types: extradural; subdural; and intraparenchymal. Prompt surgical removal of significant subdural and extradural hemorrhage is of established and widely accepted value. Intraparenchymal hemorrhage is commoner than both the other types put together and is found in >40% of severe head injuries. It is clearly associated with a worse outcome but the role for surgical removal remains undefined. Several terms are used to describe the condition including traumatic intraparenchymal hemorrhage, traumatic intracerebral hemorrhage (TICH), and contusion. Our own prospectively collected data in over 7,000 head-injured patients in Newcastle has shown that contusions are more common in older head-injured patients and can occur in patients with less severe head injury.

Surgical practice in the treatment of TICHs differs widely. Several issues inform the debate: (a) contused brain does not recover but appears as encephalomalacic brain tissue loss on convalescent phase imaging. This argues that removing TICHs does not increase tissue loss; (b) Extravasated blood is believed to be neurotoxic leading to secondary injury that may be avoided by surgical removal; (c) Larger TICHs may be associated with an ischemic penumbra of brain tissue that could be salvaged; and (d) Some TICHs expand to the point where they cause mass effect resulting in secondary brain injury.

The aim of early surgical TICH removal is to prevent secondary brain injury from these mechanisms. Use of the operation varies around the world. It is more frequently done in Asia than in Europe or North America.

There have been trials of surgery for spontaneous ICH (including the ongoing MRC-funded STICH II study (
http://research.ncl.ac.uk/stich/)) but none so far of surgery for TICH. The Cochrane Review (2nd Edition) has shown benefit from surgical evacuation for spontaneous supratentorial ICH (SICH)
[1]. There are differences in the pathogenesis, clinical behavior, and outcome for the two conditions
[2]. Patients suffering a TICH tend to be younger by about 15 years on average than patients suffering a spontaneous ICH and therefore the level of disability may have a large effect on their ability to return to work and their economic output. Traumatic ICHs are more likely to be lobar, to be superficial, and to have a medium-sized volume (25 to 65 cc). These differences between the conditions mean that we cannot derive the role of surgery for TICH from results of the 13 published trials of surgery for spontaneous ICH but the STICH trial showed a trend towards better outcome with surgery for the group of spontaneous supratentorial ICH that are most like TICH: superficial hematomas with no intraventricular bleed
[3].

We already know that surgery is effective in patients with traumatic EDH and SDH and that early surgery is better than delayed. This is not known for TICH. If early surgery is of benefit to these patients, then implementation of early referral and diagnosis with immediate treatment may reduce death and disability in this specific group of head-injured patients.

Several authors
[4-6] have compared surgery with conservative treatment in single center retrospective series and recommended surgery for larger TICHs even if patients were in an apparently good clinical state initially. Matheisen *et al.*[4] found that patients with an admission Glasgow Coma Score of at least 6 and a lesion volume of at least 20 mL who had surgery without previous neurological deterioration had significantly better outcomes than those who did not have surgery or had surgery after deterioration. None of the patients who had surgery before any deterioration died or were vegetative as opposed to 39% of those who had surgery after deterioration and 50% of those who did not have surgery. Choksey *et al.*[5] found that 38% of patients with a low GCS and a volume of the TICH >16 mL who had surgery had a poor outcome compared to 56% of those who did not have surgery. Zumkeller *et al.*[6] found that the poor outcome rate in the operated patients was 29% compared to 59% in the non-operated group. Such associations do not represent true causes and effects or treatment benefits or harm.

Boto *et al.*[7] evaluated the characteristics of severely head-injured patients with basal ganglia TICH and found that they tended to enlarge in the acute post-traumatic period. They found that patients with a TICH of >25 mL and those in whom TICH enlargement or raised intracranial pressure had occurred had the worst outcomes. They suggested that these patients might benefit from more aggressive surgical treatment.

D’Avella *et al.*[8] published a series and suggested that non-comatose patients with smaller TICHs may be treated conservatively but that surgery is indicated for patients with larger TICHs. Most of their comatose patients who were severely injured had a poor outcome whatever treatment was used.

None of these studies involved randomization into surgical and non-surgical groups. They also differed in the characteristics of the parenchymal blood. Such uncontrolled observational studies are potentially misleading and a randomized controlled trial is needed otherwise the wrong conclusion could be drawn.

Guidelines for the Surgical Management of Traumatic Brain Injury were published in 2006 in *Neurosurgery* (2006, **58:**S2-1-62). These confirm that studies in this area have been observational and there is a lack of Class 1 evidence from well-designed randomized controlled trials
[9]. Those studies that attempt to compare outcome between surgical and non-surgical groups cannot adequately control for known prognostic variables.

NICE have recommended in the Head Injury Update Full Guideline (2007) that research is needed to develop a consensus on criteria for lesions not currently considered to be surgically significant: namely TICH. This trial (STITCH(TRAUMA)) has been recommended by the latest NICE Head Injury Guideline Development Group.

This study (STITCH(TRAUMA)) is to evaluate the role of early surgical removal of traumatic intracerebral hematomas.

### Objectives

To determine whether a policy of early surgery in patients with traumatic intracerebral hemorrhage improves outcome compared to a policy of initial conservative treatment.

To assess the relative costs and consequences of early surgery *versus* conservative management in UK patients and those in a subgroup of countries covering the likely highest recruiting centers.

To confirm appropriate thresholds for intracranial pressure (ICP) and cerebral perfusion pressure (CPP) for clinical management of head-injured patients with TICH in the subgroup of patients with such monitoring.

## Methods/Design

### Trial design

The Surgical Trial in Traumatic Intracerebral Haemorrhage (STITCH(TRAUMA)) is an international multicenter pragmatic randomized parallel group trial comparing early surgical evacuation of TICH with initial conservative treatment. Only patients for whom the treating neurosurgeon is in equipoise about the benefits of early surgical evacuation compared to initial conservative treatment are eligible for the trial. An independent 24-h telephone and web randomization service based in the Aberdeen Clinical Trials Unit is used. This is backed up by 24-h availability of Trial Investigators who can advise on patient eligibility. Random allocation ensures that the two groups are balanced within a geographic region with a minimization algorithm based on age and severity. Outcome is measured at 6 and 12 months via a postal questionnaire using the extended Glasgow Outcome Scale.

Additional data is collected in those centers that practice invasive brain monitoring of intracranial pressure (ICP) and cerebral perfusion pressure (CPP) to see if there is evidence that such monitoring techniques add value to clinical decision-making. This will give an unbiased assessment of the effect of clot removal or not on ICP/CPP. This analysis will help to evaluate whether monitoring ICP/CPP provides additional information that informs better clinical management (the third objective). Such monitoring is not mandatory for a patient to be enrolled in the trial.

Relevant healthcare costs will be assessed in the UK including length of hospital stay and the costs associated with surgical treatment (theater time, consumables, overheads); healthcare resource use outside of hospital (for example, district nurse, physiotherapy) together with productivity costs arising from absence from work; and additional costs for family members through extra caring responsibilities. Consequences will be measured by combining data on quality of life, measured using the EQ-5D with survival to generate Quality Adjusted Life Years (QALYs).

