### Randomization (treatment allocation)

Before randomization, a one-page form is completed by the responsible neurosurgeon recording demographic (age, gender) and TICH characteristics (site, side, ABC measures to define volume) and status at randomization (pupils equal and reacting or not). The clinician either telephones the independent 24-h telephone randomization service or accesses the randomization website and enters the randomization information. At the end of the randomization phone call/web data entry process the neurosurgeon is informed of the patient identifier number for the trial and the treatment group the patient is allocated to. The neurosurgeon records this information on the randomization form and then faxes the form to the STITCH(TRAUMA) Office. If the site has problems contacting the randomization service they are able to contact a member of the project team using the study backup number.

The data manager checks this information against the information received from the randomization center and enters the data into an anonymized password protected database. A list of patient names and study numbers are kept in a separate file to ensure patient confidentiality is maintained.

Allocation is stratified by geographic region, with a minimization algorithm based on age group and severity (as measured by whether the pupils are equal and reacting or not) and with a random component (that is, with probability of 80%).

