### Trial interventions

The two trial interventions are: (1) early evacuation of the hematoma by a method of the surgeon’s choice (within 12 h of randomization), combined with appropriate best medical treatment; or (2) best medical treatment combined with delayed (>12 h after randomization) evacuation if it becomes appropriate later. Both groups are monitored according to standard neurosurgical practice.

If the patient is randomized to early surgery this should be undertaken as soon as possible and within 12 h of randomization.

Best medical treatment may include (depending on the practices within the center) monitoring of ICP or other modalities and management of metabolism, sodium osmotic pressure, temperature, and blood gasses.

All patients also have an additional CT scan at about 5 days (+/−2 days) to assess changes in the hematoma size with and without surgery. This will enable us to demonstrate the proportion of the clot removed by surgery or the changes in volume of the clot without surgery.

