### Statistical analysis

Analysis will be on an ‘intention-to-treat’ basis. The primary analysis will be a simple categorical frequency comparison using the uncorrected chi-squared test for prognosis-based
[13,14] favorable and unfavorable outcomes at 6 months. Patients with a good prognosis will be categorized as having a favorable outcome if they achieve good recovery or moderate disability on the Glasgow Outcome Scale. Patients with a poor prognosis will be categorized as having a favorable outcome if they achieve good recovery, moderate disability, or upper severe disability on the extended Glasgow Outcome Scale. Logistic regression analysis will be undertaken to adjust for covariates. Secondary outcomes will also be analyzed using the prognosis based method as specified in STICH
[3].

Given the likelihood of a proportion of crossovers, a secondary sensitivity analysis of per-treatment as well as an analysis considering crossovers to surgery as failed medical treatment will be undertaken. Further analyses of factors that drive crossovers as well as per-protocol and per-treatment analyses will be conducted to investigate the effect of crossovers.

Any subgroup analyses will be based on tests of interaction. The predefined subgroups (all of which will be considered exploratory, since the study is not powered for formal subgroup analyses) include the following: age; hematoma volume; Glasgow Coma Score; time from injury to randomization; severity of neurological deficit; pupils equal and reacting or not; planned method of hematoma removal; patients with invasive monitoring (ICP/CPP); anticoagulation status.

Interim analyses are conducted at intervals predetermined by the DMEC. The results of interim analyses are strictly confidential and the trial will only be stopped early if one or other treatment policy shows an advantage at a very high significance level, or if recruitment rates are unexpectedly low.

Deterministic and probabilistic sensitivity analyses will be conducted to consider the importance of individual parameters and assumptions in determining cost-effectiveness. This will include the effect of time horizon, variation in unit costs across centers, and quality of life values. Bootstrapped-generated differences in costs and effectiveness between strategies will be computed, and results presented using cost-effectiveness acceptability curves (CEACs).

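### The ICP/CPP comparison is called unbiased, but nothing fixes the monitored group before randomisation, so it and the monitored-patient subgroup are open to selection by arm

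*Protocol article*

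**What the plan says.** All references are to the protocol article.

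- **Trial design.** On the source of the data: "Additional data is collected in those centers that practice invasive brain monitoring of intracranial pressure (ICP) and cerebral perfusion pressure (CPP"). On what the data will deliver: "This will give an unbiased assessment of the effect of clot removal or not on ICP/CPP". On whether monitoring is required: "Such monitoring is not mandatory for a patient to be enrolled in the trial".
- **Trial interventions.** "Best medical treatment may include (depending on the practices within the center) monitoring of ICP or other modalities". Best medical treatment is the backbone of the conservative arm, and it is also part of the surgical arm, described as "early evacuation of the hematoma by a method of the surgeon’s choice (within 12 h of randomization), combined with appropriate best medical treatment".
- **Compliance.** ICP/CPP values are gathered in invasively monitored patients, in the same account as the clinical status recorded over the first 5 days in the trial. The stated purpose is to describe the deterioration that leads to later surgery.
- **Blinding.** Treating surgeons cannot be blinded to surgery.
- **Statistical analysis.** The predefined subgroups include "patients with invasive monitoring (ICP/CPP"). All subgroups are to be examined by interaction tests and are labelled exploratory. The Abstract also announces the analysis of monitored patients.
- **Randomization (treatment allocation).** The pre-randomisation form is summarised as demographics, haematoma characteristics and "status at randomization (pupils equal and reacting or not"). Allocation is balanced on region, age group and pupils. Monitoring appears in neither list.

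**The concern.** Randomisation protects a comparison of everyone randomised, or of a subset fixed before allocation. It does not protect a subset whose membership can depend on the arm or on what happens after allocation. ICP and CPP values exist only for monitored patients. If clinicians who know the allocation decide whom to monitor, the monitored patients in the two arms may differ in severity, and that difference would be read as an effect of clot removal.

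Two outputs are exposed: the between-arm ICP/CPP comparison that the Trial design section calls unbiased, and the interaction test for the monitored subgroup. Either could be reported as randomised evidence when it is not.

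**Working it through.** **1. Does the text fix the group before allocation?** The claim of no bias needs one of three things: monitoring of every patient, monitoring status settled before allocation, or monitoring decided in the same way in both arms. The first is excluded because monitoring is not mandatory. The second is not stated anywhere. The third cannot be assumed, because monitoring is a discretionary part of the treatment that follows allocation and the treating surgeons are unblinded. The claim is therefore not supported by the design as described.

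**2. The plan's own figure, for scale.** The article gives no figure for the ICP/CPP comparison. Its target effect is 10 points (50% versus 60% favourable), with a total of 776:

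n per arm = [1.960·√(2·0.55·0.45) + 0.842·√(0.50·0.50 + 0.60·0.40)]² / 0.10² = (1.379 + 0.589)² / 0.01 = 387.3, so 388 per arm and 776 in total. This reproduces the stated figure.

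**3. Equal monitoring rates, different selection.** Every input here is an assumption. Surgery has no effect. Half the patients are severe (35% favourable) and half mild (65% favourable). Each arm monitors 50% of its patients. The surgical arm monitors regardless of severity, so its monitored and unmonitored patients are both 0.5·0.35 + 0.5·0.65 = 50% favourable. The conservative arm monitors a share a of severe patients and 1 − a of mild patients:

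- monitored: 0.35a + 0.65(1 − a)
- unmonitored: 0.35(1 − a) + 0.65a

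| a | Conservative, monitored | Spurious surgical benefit, monitored | Conservative, unmonitored | Spurious interaction |
|---|---|---|---|---|
| 0.5 | 50% | 0 points | 50% | 0 points |
| 0.6 | 47% | 3 points | 53% | 6 points |
| 0.7 | 44% | 6 points | 56% | 12 points |
| 0.8 | 41% | 9 points | 59% | 18 points |

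The last row in full: (0.5·0.8·0.35 + 0.5·0.2·0.65) / 0.50 = 0.205/0.50 = 41% monitored, and (0.035 + 0.26)/0.50 = 59% unmonitored. The interaction is (50 − 41) − (50 − 59) = 18 points. Because both arms monitor 50%, monitoring rates by arm would not reveal this.

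**4. Different monitoring rates, same kind of selection.** This is a simulation of 2,000,000 patients, again on assumed inputs with no true effect. Severity U is standard normal. ICP = 18 + 6·(0.6U + 0.8·noise) mmHg. The probability of a favourable outcome is 1/(1 + e^U), which is 50% overall. A patient is monitored when 0.7U + √0.51·noise exceeds the cut-off that gives the stated rate.

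| Monitored, surgery / conservative | ICP difference (surgery − conservative) | Favourable-outcome difference |
|---|---|---|
| 50% / 50% | 0.0 mmHg | 0.0 points |
| 60% / 50% | −0.39 mmHg | +2.3 points |
| 70% / 50% | −0.76 mmHg | +4.6 points |
| 80% / 40% | −1.55 mmHg | +9.2 points |
| 90% / 30% | −2.42 mmHg | +14.3 points |

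The last row is an extreme contrast, shown for completeness. Exchanging the arms reverses every sign, so the direction is not known in advance either.

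**The case against.** **Timing is not stated.** The article does not say when monitors are placed. Entry is allowed up to 48 h after injury, so some patients may already be monitored, and for them no selection by arm arises. This stands. A reader might infer that monitors are inserted at operation and that monitoring therefore must differ by arm. The article does not say so.

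**Centre practice precedes allocation.** Trial design speaks of centres that monitor, and Trial interventions refers to centre practice. Restriction to such centres would not bias a comparison of all their randomised patients. That is correct, but it does not rescue the claim. ICP/CPP values exist only for the patients actually monitored, and the subgroup is worded by patient, not by centre.

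**The subgroup is already exploratory.** The label limits how much will be claimed. It is justified in the text by lack of power, and it does not repair a subgroup formed by care after allocation. The Trial design sentence does not carry the label.

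**The baseline form may be abbreviated.** The article's list also leaves out time of injury, although the 48 h limit is an entry criterion. The absence of monitoring from that list is therefore weak evidence that it goes unrecorded, and the point does not rest on it. For the same reason the list cannot be used against the planned-method subgroup, where the word planned itself suggests intent before treatment.

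**The third objective is a different analysis.** A reader might infer that it fails too. Under Objectives it concerns ICP and CPP thresholds, and Statistical analysis assigns these to receiver-operating curves. That is not a between-arm contrast. Trial design links the two only loosely.

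**Conclusion.** The point holds in a limited form. The article asserts an unbiased between-arm assessment, and predefines a subgroup, in a group whose membership may be shaped after allocation. Nothing in the article restricts either analysis to patients whose monitoring was fixed beforehand.

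The bias is possible, not demonstrated, since no document figure shows that monitoring differs by arm. Its size depends wholly on the assumptions: none under identical selection, about 2 points at 60%/50%, and about 9 points either at 80%/40% or at equal rates with strongly severity-driven monitoring in one arm only. A reader might take 9 points, close to the 10-point target, as the expected bias. It is the upper end of an illustrative range, not an estimate.

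The primary intention-to-treat analysis and the sample size are unaffected. The threshold work is not affected as a randomised contrast, because it is not one.

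**What to change.** 1. Define the monitored subgroup and the between-arm ICP/CPP comparison by monitor in place at randomisation (yes/no), recorded before allocation. For outcome comparisons only, the centre's routine monitoring policy, declared in advance, is an alternative, provided all randomised patients of those centres are analysed. It does not suffice for ICP/CPP values, which exist only for patients actually monitored.
2. In Trial design, replace the word unbiased with exploratory.
3. In Statistical analysis, label any comparison of all monitored patients as non-randomised. Report with it, by arm, the monitoring rate and the baseline severity of monitored patients. The rate alone is not enough, as the equal-rate calculation shows.

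The cost is one baseline item if it is not already collected, some changes of wording, and a somewhat smaller subgroup. No patient's care changes.
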